### 2.4 Intervention

We plan to include 200 patients for analysis, with 100 in the experimental group and 100 in the control group. Both groups will undergo PTC drug sensitivity testing and whole exome sequencing (WES). For the experimental group, doctors will select adjuvant chemotherapy regimens on the basis of the PTC drug sensitivity test results. For the control group, doctors will determine adjuvant chemotherapy strategies on the basis of their clinical experience. The PTC drug sensitivity and WES results will be documented for humanitarian treatment reference after the study concludes or if patients withdraw from the study.

### 2.5 Therapeutic schemes

#### 2.5.1 PTC drug sensitivity test.

Upon receiving the tumor tissue, the laboratory will verify the sample number and establish a sample file via the laboratory management system for data file management. After laboratory tests are conducted on the sample status (including temperature, time in vitro, and presence of leakage), sample processing and cultivation will be performed. After 2–7 days of cultivation, the formation of PTC clones will be observed via bright field microscopy. If PTC clones fail to form within 7 days, cultivation will be declared unsuccessful, and the patient will be withdrawn. If PTC clones are formed, open field photos will be retained to check for bacterial, fungal, and mycoplasma infections in the culture. Samples identified as negative will be subjected to drug sensitivity experiments [14].

We will test four commonly used adjuvant chemotherapy regimens in clinical practice [19]: fluorouracil+formyltetrahydrofolate (5-RU) [7], oxaliplatin+5-fluorouracil+formyltetrahydrofolate (FOLFOX) [20], irinotecan+5-fluorouracil+formyltetrahydrofolate (FOLFORI) [21,22], and cetuximab+5-fluorouracil+formyltetrahydrofolate [23,24]. For the screening experiment, a 96-well plate will be used, and each experimental group will be equipped with three parallel wells to ensure the reliability of the experimental data. Each sample will be collected twice, once after 0 days of dosing and once after 7 days of dosing. The automatic scanning system will be used to identify the number and area of all PTC clones in the hole. The area ratio of PTC clones (i.e., residual cell viability) after and before dosing will be calculated via the $p_{Ai}=\frac{S_{Ai,t}}{S_{Ai,t0}}$, $p_{A}=\frac{1}{n}\sum_{i=1}^{n}p_{Ai}$ formula [25], and the interpretation criteria are shown in Table 1. The higher the score is, the better the drug’s efficacy in killing tumors, and higher-scoring regimens are more recommended.

**Table 1 pone.0326760.t001:** Criteria for Judging the Drug Sensitivity of PTCs.

Lethality level	Lethality cell percent (%)	Remaining cell percent (%)
**Strong killing effect**	>0.7	0-0.3
**Effective killing effect**	0.3-0.7	0.3-0.7
**Stable**	0.1-0.3	0.7-0.9
**Drug resistant**	0-0.1	0.9-1
**Strongly drug resistant**	0	1

#### 2.5.2 Whole-exome gene sequencing (WES).

We will perform whole-exome gene testing on the patient’s histological specimens. The specific testing procedure is as follows: 1) tumor-targeted genes, including point mutation, insertion/deletion, fusion, and copy number variation analyses, will be used to predict the effectiveness of targeted drugs, tumor molecular subtypes, and patient prognosis; 2) a total of 145 tumor chemotherapy-related genes will be used to predict the effectiveness and side effects of commonly used chemotherapy drugs; 3) tumor mutational burden and microsatellite instability will be used to predict the efficacy of immunotherapy drugs; and 4) tumor susceptibility genes will be used to predict the genetic risk of multiple tumors.

### 2.6 Follow-up and endpoints

The patient’s age, sex, pathological type, treatment plan, treatment drug dosage and cycle, pretreatment clinical staging, imaging results, oncological outcomes, etc., will be recorded. After discharge, patients will be reexamined in the outpatient clinic two to three weeks postsurgery to record any short-term complications and will subsequently be followed up for five years. Within the first two years postsurgery, patients will undergo clinical examinations every three months, including a digital rectal examination (DRE), examination of tumor markers such as CEA and CA19−9, chest X-ray (front and side views), and abdominal ultrasound (liver, gallbladder, pancreas, spleen, and kidney). Within two to three years postsurgery, patients will be followed up every six months. After three years, annual follow-ups will be conducted, which will include chest–abdomen–pelvis enhanced CT scans, rectal MRI or rectal ultrasound, and colonoscopy.

Follow-up will be conducted through doctor outpatient reviews as well as specialized follow-up personnel via phone, e-mail, text and other means. During the follow-up process, detailed records of the patient’s status (tumor-free survival, local recurrence, distant metastasis, death, etc.) will be recorded. The time, location, and cause of the endpoint event will also be recorded.

The main endpoint of the study is the 3yDFS rate. The secondary endpoints of the study are as follows: 1) consistency between the test results of the extended medication regimen and the clinical outcomes; 2) time to progression (TTP), objective response rate (ORR), progression-free survival (PFS), and overall survival (OS); and 3) consistency of gene mutation status, tumor mutation burden (TMB), microsatellite instability (MSI), and mismatch repair (MMR) status with clinical prognosis.

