### 2.2 Participants and recruitment

We will recruit a total of 200 patients with clinically staged T3-4N0M0 or TanyN + M0 CRC from 9 hospitals in China. The study will document the demographic data, clinical and pathological features, imaging findings, operative results, and oncological outcomes of all enrolled patients.

At this point, we have included all patients clinically staged as T3-4N0M0 or TanyN + M0 in the candidate pool and obtained signed consent forms for the study, but the patients have not yet been enrolled. If patients are determined to require radical resection for CRC after clinical diagnosis and treatment, we will collect approximately 50 mg of fresh cancer tissue with abundant blood vessels from the excised tumor specimens in the operating room after the completion of radical surgery. The samples will be placed in preservation tubes and transported to the laboratory at 4 °C, where PTC model construction will be completed. Upon receipt of the surgical pathology results, if patients indeed meet the criteria for adjuvant chemotherapy, we will select patients on the basis of the inclusion and exclusion criteria.

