#### 2.2.1 Inclusion criteria.

The inclusion criteria are as follows: 1) patients with histologically confirmed CRC; 2) baseline clinical stage of cT3-4N0M0 or cTanyN + M0; 3) CRC patients requiring adjuvant treatment after radical surgery and not receiving neoadjuvant treatment; 4) at least one evaluable tumor lesion; and 5) Eastern Cooperative Oncology Group (ECOG) performance status ≤ 2.

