#### 2.2.2 Exclusion criteria.

The exclusion criteria are as follows: 1) patients with distant metastases; 2) patients unable to obtain tumor samples; 3) pregnant and lactating women; 4) patients with poor compliance; 5) patients with severe cardiovascular and cerebrovascular complications unable to receive chemotherapy or targeted therapy; 6) patients previously diagnosed with other malignant tumors; 7) patients with severe mental and neurological disorders; and 8) patients deemed unsuitable for participation in this study by researchers.

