#### 2.7.3 Statistical methods.

Local recurrence is defined as tumor recurrence in the lumen or in the mesorectum and must be confirmed by a pathological biopsy. A distant metastasis is defined as a metastasis that is discovered in the liver, lung, bone, or other sites by CT, MRI, or radionuclide scanning, with or without pathological examination. Disease-free survival (DFS) is defined as the absence of local recurrence, distant metastasis, and death from any cause. Overall survival (OS) is defined as the absence of death from any cause. The duration of follow-up will be calculated from the date of surgery to the event of interest or the last follow-up date.

To determine the consistency between the PTC drug sensitivity results and clinical outcomes, the following methods will be employed (Table 2): positive consistency rate = a/(a + c) × 100%; negative consistency rate = d/(b + d) × 100%; overall consistency rate = (a + d)/(T1) × 100%; sensitivity = a/(a + b) × 100%; and specificity = d/(b + d) × 100%.

**Table 2 pone.0326760.t002:** Consistency test of recurrence and metastasis cases.

Drug sensitivity test	Clinical efficacy		Sum
	CR + PR	SD + PD	
**Effective**	a	B	a + b
**Invalid**	c	D	c + d
**Sum**	a + c	b + d	T1

The results will be presented as median values or means ± standard deviations for continuous variables and as numbers (percentages) for categorical variables. The t test and Wilcoxon rank sum test will be used to compare continuous variables, and chi-square analysis/Fisher’s exact test will be used to compare categorical variables. Survival analysis will be conducted using the Kaplan-Meier curves. Log-rank test to compare the primary endpoint between different arms in the presence of censoring. A P value of 0.05 or less is considered statistically significant. All the statistical tests will be two-sided. All analyses will be performed using SPSS Version 26.0 (SPSS Inc., Chicago, IL).

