In addition, researchers have transplanted tumor tissue into immunodeficient mice and established a PDX model in which mice are used instead of humans for drug sensitivity testing [13,42]. However, owing to limitations such as success rates (50% or even lower), testing cycles (more than 4 months), and high costs, it is difficult to apply this model in clinical practice.

As a novel in vitro tumor model, PTCs can form 3D microspheres by cutting, digesting, and proliferating samples from patients and then self-assembling tumor cells and tumor stromal cells, which are highly similar to the original tumor tissue in terms of morphology, pathological features, genetic background, and other dimensions [14]. This technology is an efficient, accurate, and short-cycle in vitro drug sensitivity detection system. PTC drug sensitivity detection technology overcomes the bottleneck issues of in vitro model technologies in clinical applications, achieving trace amounts, safety, accuracy, and timeliness, and has great potential in clinical translational applications.

For patients after tumor surgery, it is difficult to evaluate whether adjuvant chemotherapy drugs can effectively kill the tumor, as there is no longer any visible tumor on imaging. On the basis of PTC technology, this study will conduct drug sensitivity tests in vitro after surgery and before adjuvant therapy to evaluate the sensitivity of tumors to chemotherapy drugs to implement precise and personalized treatment for patients. Ultimately, our goal is to provide personalized adjuvant chemotherapy regimens for patients with colorectal cancer, thereby increasing survival benefits.

Previous studies on PTC technology have been cases reports, retrospective or small-scale single center observational studies. This study is the first multicenter, prospective randomized controlled trial to explore the sensitivity of adjuvant chemotherapy regimens for CRC using PTC as a new technology. If this method appears beneficial, this study can help to generate preliminary guidelines for postoperative chemotherapy management in CRC patients. We will disseminate the results of this study to international journals and conferences.

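### ORR and the Table 2 consistency rates require measurable tumour during adjuvant treatment, which radically resected M0 patients do not have

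*Protocol article*

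**What the plan says.** All references are to the protocol article.

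- **Population.** Section 2.2.1 enrols "CRC patients requiring adjuvant treatment after radical surgery and not receiving neoadjuvant treatment". Section 2.2.2 excludes "patients with distant metastases". Section 2.2 places selection after the operation: "Upon receipt of the surgical pathology results, if patients indeed meet the criteria for adjuvant chemotherapy, we will select patients".
- **Lesion criterion.** Section 2.2.1 also requires "at least one evaluable tumor lesion", without saying when it is judged.
- **Endpoints.** Section 2.6 lists, first among the secondary endpoints, "consistency between the test results of the extended medication regimen and the clinical outcomes", and second, "time to progression (TTP), objective response rate (ORR), progression-free survival (PFS), and overall survival (OS".
- **Consistency rates.** Section 2.7.3 takes all rates from Table 2. Its rows are Effective and Invalid, its columns are CR + PR and SD + PD, and its caption is "Consistency test of recurrence and metastasis cases".
- **Assessability.** Section 3 says it is hard to judge whether adjuvant drugs kill the tumour after surgery, "as there is no longer any visible tumor on imaging".
- **Outcomes collected.** Section 2.6 records tumour-free status, local recurrence, distant metastasis and death. Section 2.7.3 defines recurrence, metastasis, DFS and OS. Nothing maps these to CR, PR, SD or PD.

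**The concern.** CR, PR and SD describe what happens to a lesion under the treatment being judged. Here the lesion is removed before that treatment starts, and the protocol says so. ORR then has no assessable patients, and the columns of Table 2 cannot be filled for the adjuvant regimen that the PTC assay was meant to predict.

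This is not detail left to a fuller document. The article itself fixes the table, its columns and its formulas, and they do not suit this population.

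Consistency between PTC results and clinical course is a declared aim of the study (Abstract, sections 1 and 2.1). If the definition cannot be applied, a mapping from follow-up status to the table will have to be made up later, in an unblinded trial and possibly with outcomes known.

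**Working it through.** **Inputs.** From section 2.7.1: 3-year DFS 75%, margin 20 percentage points, two-sided alpha 0.05, power 80%, dropout 20%, 200 patients in all. From section 2.7.3: Table 2 and its formulas. Assumed, because the documents give no figure: a DFS range of 65% to 85%, and a share testing Effective of 50%, 70% or 90%.

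**1. The plan's own figure.** n per group = 2 × 0.75 × 0.25 × (1.960 + 0.842)² / 0.20² = 73.6, rounded up to 74. This matches the plan. With 20% dropout, 74 / 0.80 = 92.5, so 93, and the chosen 100 covers it. The sample size is not in dispute; the calculation only confirms that 75% is the planning rate.

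**2. Who could have a lesion.**
- Event-free at 3 years: 200 × 0.75 = 150 (130 to 170 over the assumed range). These patients have no tumour and no response category.
- DFS event by 3 years: 200 × 0.25 = 50 (30 to 70 over the range). With 20% dropout, 160 × 0.25 = 40.
- DFS events include deaths without recurrence, so 50 is an upper figure for recurrence and metastasis cases at the planning rate.

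**3. Table 2 as captioned, with the adjuvant regimen as reference.** Every patient who enters has relapsed after that regimen, so none is a responder and a = c = 0. Take T1 = 50.

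| Share testing Effective (assumed) | b | d | Positive consistency a/(a+c) | Negative consistency d/(b+d) | Overall (a+d)/T1 | a/(a+b), labelled sensitivity |
|---|---|---|---|---|---|---|
| 50% | 25 | 25 | 0/0 | 50% | 50% | 0 |
| 70% | 35 | 15 | 0/0 | 30% | 30% | 0 |
| 90% | 45 | 5 | 0/0 | 10% | 10% | 0 |

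Overall consistency is simply the proportion tested Invalid. It cannot show whether the assay separates patients who relapse from those who do not, because the latter are absent.

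**4. Table 2 with post-relapse treatment as reference.** Lesions can then exist, and CR or PR can occur. But the response is to a later treatment in a different disease state, and the article defines no such response assessment.

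**5. A caution for the repair.** If all 200 patients enter and the columns become 3-year DFS status, a test that always says Effective gives a = 150, b = 50, c = d = 0. Overall agreement is 150/200 = 75%. Chance agreement is 1 × 0.75 + 0 × 0.25 = 75%, so kappa = 0. Raw agreement alone would flatter the assay.

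**The case against.** **The aim is not lost.** The objective is worded as consistency with prognosis or outcomes, and recurrence, metastasis and death are all recorded. This stands. A reader might infer that the study aim cannot be answered, but the fault lies in how one table and one endpoint are defined, and DFS data already planned can repair it.

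**A post-relapse analysis may be intended.** The caption, the undefined phrase about an extended medication regimen in the first secondary endpoint, and the retention of PTC results for later treatment reference (section 2.4) all leave room for this. It is a possible reading, but the article does not set it out and it would not test the adjuvant choice that was randomised.

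**TTP and PFS can be computed** if recurrence counts as progression. This stands. They are undefined here and may duplicate DFS, but only ORR clearly lacks measurable disease.

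**The evaluable-lesion criterion may refer to the preoperative tumour**, as the baseline stage criterion does. This stands. One might infer that no resected patient is eligible; the text supports only an ambiguity of timing.

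**Arms and the Invalid row.** A reader might infer that Table 2 pools the arms, or that its Invalid row is nearly empty in the experimental arm. Neither is in the text. T1 is only a table total, and regimens are ranked relative to one another, so a patient's best regimen could still be one the tumour resists.

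**The 3-year horizon is not written into Table 2.** Correct. Follow-up lasts five years, and the 5-year DFS of 55–65% cited in section 1 would imply 70 to 90 events in 200. The table would be larger but still selected on the outcome.

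**Conclusion.** Wrong as written, for secondary endpoints only. ORR in the adjuvant phase and the CR + PR versus SD + PD consistency rates give no valid result for the regimen under test. Under the caption's restriction, the positive consistency rate is undefined, a/(a+b) is 0 whatever the assay shows, and overall consistency equals the share tested Invalid. At the planned 75% 3-year DFS the captioned table would hold at most about 50 of 200 patients by 3 years.

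The a = c = 0 result assumes that the adjuvant regimen is the treatment being judged. The exact percentages depend on the assumed share testing Effective; the structural result does not.

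**What to change.** 1. Replace the Table 2 columns by DFS event-free at 3 years and DFS event within 3 years, for the regimen actually received, in all patients with a valid PTC result. Remove the restriction in the caption. Handle patients censored before 3 years by Kaplan-Meier estimates or inverse-probability weighting.
2. Report by arm, because in the experimental arm the PTC result drives the choice of regimen (section 2.4).
3. Alongside raw agreement, give a chance-corrected measure or DFS by PTC result.
4. Delete ORR for the adjuvant phase, or confine it to a defined exploratory description after relapse. Define TTP and PFS relative to DFS, or drop them as redundant.
5. Reconcile the evaluable-lesion criterion with selection after resection by stating when the lesion is assessed.

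**Cost.** Wording only, with no new data. Event-free status also reflects cure by surgery alone, so the revised table measures association with prognosis, not pure drug response. Estimates by arm rest on about half the patients each and are less precise.

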### 2.7 Statistical analysis

#### 2.7.1 Sample size.

Our study is a noninferiority study. With a bilateral α = 0.05, a test efficacy of 1-β = 80%, a 3-year disease-free survival rate of 75%, and a noninferiority threshold of 20%, the estimated minimum sample size for each group is 74. Considering a dropout rate of 20% (according to EMEA [26], ICH [27], and FDA [28] guidelines and previous studies [29]), we ultimately decided to include 100 patients in each group, totaling 200 patients across both groups.

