## 1 Background

Colorectal cancer (CRC) is a common gastrointestinal malignancy that seriously endangers human health. According to cancer statistics 2023 [1], CRC has become the third most common cancer in terms of both incidence and mortality rates. Approximately 25–30% of stage II CRC patients experience recurrence and metastasis within 5 years after surgery, whereas approximately 50–60% of stage III CRC patients experience recurrence and metastasis within 5 years after surgery [2,3]. In addition, 45–50% of patients with stage II-III disease develop liver metastases within two years after primary resection [4,5]. As the main adjuvant treatment for CRC surgery, multiple international clinical studies have shown that surgery combined with adjuvant chemotherapy can achieve a total 5-year survival rate of 60–70% and a total 5-year disease-free survival rate of 55–65% for high-risk stage II and stage III patients [6,7].

However, CRC is a malignant tumor with significant heterogeneity [8,9], and there are significant individual differences in drug sensitivity among patients. Even patients with the same pathological type and clinical stage who receive the same treatment plan have different prognoses and outcomes [10]. The selection of adjuvant chemotherapy regimens for different subgroups of patients remains controversial. Therefore, constructing a model that can accurately predict drug efficacy and guide personalized treatment for patients is one of the strategies for achieving precision treatment of CRC. Scientists have been dedicated to developing in vitro models for drug sensitivity testing over the past century, including cell lines, primary tumor cells [11], patient-derived organoids (PDOs) [12], and patient-derived tumor xenograft (PDX) mice [13]. However, owing to issues such as standardization, accuracy, and cycle, these methods have certain limitations in clinical application and struggle to achieve true clinical translation.

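### The trial is sized for noninferiority at a 20-point margin, but the only primary comparison described is a log-rank test without a margin, and a noninferiority pass could not support the benefit aim

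*Protocol article*

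**What the plan says.** Section 2.7.1 declares "Our study is a noninferiority study". Its inputs are "With a bilateral α = 0.05", "a test efficacy of 1-β = 80" percent, "a 3-year disease-free survival rate of 75" percent and "a noninferiority threshold of 20" percent. The result is at least 74 per group, raised to 100 per group for 20% dropout.

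Section 2.7.3 plans Kaplan-Meier curves and a log-rank test between the arms for the primary endpoint. All tests are two-sided and judged at P of 0.05 or less. No comparison of a confidence limit with 20 points is described, and no order between noninferiority and superiority.

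Section 2.1 gives improved clinical benefit as the end purpose. Section 3 puts the ultimate goal as "personalized adjuvant chemotherapy regimens for patients with colorectal cancer, thereby increasing survival benefits" and describes the use of the result conditionally: "If this method appears beneficial, this study can help to generate preliminary guidelines for postoperative chemotherapy management in CRC patients".

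**The concern.** Three parts of the article point to different questions. The sample size asks whether PTC guidance is less than 20 points worse. The analysis asks whether the arms differ at all. The stated purpose asks whether PTC guidance is better.

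The practical risk is in reading the result. A non-significant log-rank test in a trial labelled noninferiority invites the reading that noninferiority has been shown, which it has not. A formally correct noninferiority pass at 20 points could in turn be carried into language about benefit and guidelines, although it is compatible with a worse DFS in the guided arm.

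**Working it through.** **Inputs (section 2.7.1).** Two-sided alpha 0.05 (0.025 one-sided for noninferiority), power 80%, 3-year DFS 75%, margin 20%, dropout 20%. Only one DFS rate is given, so equal true rates are assumed.

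**1. Reproduce the plan's figure.** n = 2 × 0.75 × 0.25 × (1.960 + 0.842)² / margin².
- Absolute 20 points: 0.375 × 7.849 / 0.04 = 73.6, so 74. This matches.
- Relative 20%, i.e. 15 points: 0.375 × 7.849 / 0.0225 = 130.8, so 131. This does not match.
- Superiority formula, 75% against 55%: 89. This does not match.

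The margin is therefore 20 absolute points. Dropout: 74 / 0.8 = 92.5, so 93, which 100 per group covers. With 20% loss, 80 per group remain, so 80-100 is used below.

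**2. The margin as a hazard ratio (proportional hazards).** ln(0.55) / ln(0.75) = 2.08. The 3-year event risk goes from 25% to 45%. With a control rate of 70% the ratio is ln(0.50) / ln(0.70) = 1.94; with 80% it is ln(0.60) / ln(0.80) = 2.29.

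**3. What a noninferiority pass allows.** Control observed at 75%, pass if the lower 95% limit is above -20 points, binomial standard errors, whole patients.
- 80 per arm, guided arm 56/80 = 70%: SE = √((0.1875 + 0.2100)/80) = 0.0705; lower limit = -5.0 - 13.8 = -18.8. Passes. At 55/80 the lower limit is -20.1, which fails.
- 100 per arm, guided arm 68/100: SE = √((0.1875 + 0.2176)/100) = 0.0636; lower limit = -7.0 - 12.5 = -19.5. Passes.

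An observed loss of 5 to 7 points therefore still meets noninferiority.

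**4. Why a difference test cannot stand in for it.** Illustration with 80 per arm, 60/80 = 75% against 52/80 = 65%: SE = √((0.1875 + 0.2275)/80) = 0.0720; z = 0.10 / 0.0720 = 1.39, P about 0.17. The 95% interval is -24.1 to +4.1 points. The difference is not significant, yet a loss beyond 20 points is not excluded. This uses 3-year proportions without censoring as a stand-in for the log-rank test, but the logic is the same.

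**5. Power.** Noninferiority at 20 points with equal rates: Φ(0.20/√(0.375/n) - 1.96) = 83% (n = 80) and 90% (n = 100). Superiority for 85% against 75%: Φ(0.10/√((0.1875 + 0.1275)/n) - 1.96) = 36% (n = 80) and 43% (n = 100). A pooled-variance formula gives 35% and 42%.

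**The case against.** A first objection is that the article condenses a fuller protocol, and a statistical analysis plan may hold the noninferiority interval and the reason for the margin. This stands for the reason: its absence here is no finding. It does not remove the main point. The article does name a primary comparison and a significance rule, and these do not fit its own sample-size section.

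Secondly, section 2.7.3 may be said to provide for benefit already. That is right. A reader might infer that the plan has no superiority step, but a two-sided log-rank test is a test of difference, and a significant result favouring PTC guidance would support benefit. What is missing is its relation to the noninferiority objective.

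Thirdly, a reader might infer that the article already concludes PTC guidance is beneficial. It does not: the guideline sentence is conditional, and the abstract and section 1 describe the aim mainly as consistency between test results and prognosis. Improved benefit is the end purpose, not the only aim.

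Fourthly, a reader might call the margin wrong because 55% at three years equals the lower end of "a total 5-year disease-free survival rate of 55–65% for high-risk stage II and stage III patients" in section 1. The time points differ, so the comparison does not calibrate the margin. A smaller margin would be a trade-off in power, not a correction. One might also argue that any harm is concentrated in patients whose regimen PTC actually changes; the article does not say how many would receive the same regimen in either arm, so no figure can be put on this.

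**Conclusion.** The concern holds as a conflict between sections 2.7.1 and 2.7.3 and as a limit on what a pass can mean. The sizing is for a 20-point margin (hazard ratio about 2.1; 1.9 to 2.3 for control rates of 70-80%), while the only primary comparison described has no margin and cannot establish noninferiority. A noninferiority pass would exclude only a loss of 20 points or more. It could occur with an observed loss of 5 to 7 points and so could not support the benefit aims. Benefit could be shown by a difference test, but with only about 36-43% power for a 10-point gain.

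These figures assume a control rate of 75%, proportional hazards for the hazard ratio, and 80-100 evaluable patients per arm. The 10-point gain is illustrative and not a figure from the article.

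**What to change.** Keep 200 patients and amend the text.

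1. In section 2.7.3, make the primary analysis the two-sided 95% confidence interval for the difference in Kaplan-Meier 3-year DFS, PTC-guided minus control. Declare noninferiority if the lower limit is above -20 points. Only then test superiority on the same interval, declared if the lower limit is above 0. The fixed sequence costs no alpha. Keep the log-rank test as supportive.
2. In sections 2.7.1 and 3, state that a noninferiority pass excludes only a loss of 20 points or more (hazard ratio about 2.1). Reserve statements of benefit and guideline use for a superiority result, and give the superiority power for a 10-point gain as about 36-43%.

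The cost is a narrower claim and a less favourable stated power; no patients or data fields are added. The enrolment deadline is September 1, 2025, and 3-year outcomes of late enrollees mature roughly three years later, so the change can still precede the primary analysis. Because the trial is not double-blind, the amendment should be dated before any comparison of outcomes by arm.
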